# Efficacy of Tuina in patients with chronic low back pain: study protocol for a randomized controlled trial

**DOI:** 10.1186/s13063-020-4198-2

**Published:** 2020-03-17

**Keywords:** Low back pain, Efficacy, Randomized controlled trial, Tuina, Health care education

## Abstract

**Background:**

Low back pain is a common reason for medical care and carries a heavy social burden. The efficacy of Tuina or health care education for low back pain has been evaluated in previous systematic reviews. However, there is no evidence to support the superiority of one form of treatment over another. The aim of this study is to compare the efficacy of Tuina with health care education in the management of low back pain.

**Methods/design:**

This study is a randomized controlled trial with parallel-group design including two groups: a Tuina group and a health care education group. A total of 160 eligible participants will be randomly assigned to the groups in a 1:1 ratio. The interventions of both groups will last for 20 min and be carried out twice each week for a period of 12 weeks. The primary outcome is the Oswestry Disability Index. The secondary outcomes include a visual analogue scale and the 36-item Short Form Health Survey. They will be assessed at baseline, at the end of the intervention every month, and during 6 months and 9 months of follow-up by repeated measures analysis of variance. The significance level is 5%. The safety of Tuina and health care education will be evaluated after each treatment session. This study will focus on the value of Tuina and health care education for low back pain and will highlight any differences in the efficacy of the treatments.

**Discussion:**

This study will evaluate the efficacy and safety of Tuina intervention for low back pain, which could provide reliable evidence for clinical decision making for patients with low back pain.

**Trial registration:**

Chinese Clinical Trial Registry, ChiCTR1900022656. Registered on 23 April 2019.

## Background

Low back pain is a common symptom in today’s society. It causes serious health and economic burdens. A study showed that the health cost of low back pain was increasing in every year, and the number of persons with disability due to low back pain increased by 54% between 1990 and 2015 [1]. In high-income countries, the highest point prevalence of low back pain has reached 32.9% [2]. According to the epidemiologic data of low back pain in Asia, it was defined as a health problem associated with functional limitations and financial burden [3, 4].

Low back pain can be attributed to excessive physical exertion or trauma, resulting in damage or degradation of the vertebrae, intervertebral discs, or spinal muscles. Now, we focus more on nonspecific low back pain, which typically can account for 90% of the patients [5]. The duration of pain persists for at least 3 months and must meet the International Classification of Diseases, 11th Revision (ICD­11), criteria for chronic primary pain [6]. Owing to the considerable pain and cost associated with chronic pain, some interventions must be applied to prevent its exacerbation [7].

A treatment option for individuals with low back pain is a risk stratification approach depending on screening tools such as the Orebro Musculoskeletal Pain Screening Questionnaire [8] and the STarTBack tool [9], which aim to limit progression to chronic low back pain. With a high risk, regardless of the potential harm with some pain medicines, opioids [10] and nonsteroidal anti-inflammatory drugs [11] will be used to control the condition when it does not respond to nonpharmacological treatments [12]. Surgery will also be used to relieve the compression of nerve roots caused by degenerative disc disease [13]. However, some guidelines have endorsed the cautious use of medication and surgery and take nonpharmacological and noninvasive treatments as a first-line treatment, including routine health education, exercise, psychotherapy, and physical therapies, owing to the risk of trauma and the cost [14–17]. A relatively new and promising approach in the health care education of low back pain has focused on the neurobiology and neurophysiology of pain, which attempts to help the patients understand that pain and tissue injury are different constructs [18, 19]. In addition, education is composed of the factors that affect the occurrence of the disease, including weight, occupation, and exercise style; explanation of the natural development process and harm of the disease; and explanation of the planning and prognosis of disease treatment. For patients with chronic low back pain, several studies have shown favorable outcomes following health care education in patients with chronic pain in terms of pain relief and improved physical performance [20–22]. It can also reduce emotional distress and subsequent health care use [23, 24].

Additionally, some systematic reviews showed a moderate level of evidence for the clinical efficacy of manual therapy, massage, and spinal manipulations in patients with low back pain [25–27]. Tuina, one of the key noninvasive therapies of traditional Chinese medicine, is a Chinese manual manipulation. It has been used for thousands of years in China. Some studies showed the potential effect of Tuina for chronic neck pain [28], but more clinical trials are required to provide evidence of Tuina for low back pain. Health care education has also shown promise in previous reviews to improve pain and disability in chronic low back pain [29, 30]. Therefore, this study was designed to compare the efficacy of Tuina with health care education for patients with low back pain.

## Methods/design

### Study design

This study is a single-center, assessor- and analyst-blinded randomized controlled trial conducted in Shanghai, China, at Yueyang Hospital of Integrated Traditional Chinese and Western Medicine affiliated with Shanghai University of Traditional Chinese Medicine. In total, 160 patients will be recruited and randomly assigned to a Tuina group and a health care education group in a 1:1 ratio. This trial protocol was approved by the Ethics Committee of Yueyang Hospital of Integrated Traditional Chinese and Western Medicine affiliated with Shanghai University of Traditional Chinese Medicine (project number 2019-035). It is registered with the Chinese Clinical Trial Registry (ChiCTR1900022656). Written informed consent will be provided by all patients before the screening. The interventions will be given twice per week for 3 months. We will ask some researchers who are blinded to assignment to accomplish the outcome assignment and statistical analyses independently. The trial flowchart and study design are shown in Figs. 1 and 2, respectively.

**Fig. 1 Fig1:**
[figure not shown]
Flowchart of the study. A total of 180 participants will be randomized to the two groups. The interventions will last for 20 min and will be conducted two times per week for 12 weeks. The study period will consist of the baseline, 3 months of treatment, after treatment, and 3- and 6-month follow-up. *ODI* Oswestry Disability Index, *SF-36* 36-Item Short Form Health Survey, *VAS* Visual analogue scale

**Fig. 2 Fig2:**
[figure not shown]
Study schedule

### Participant recruitment

Patients with chronic low back pain consistent with the disease definition in the ICD-11 will be recruited. The participants are outpatients and inpatients in Tuina departments of Yueyang Hospital of Integrated Traditional Chinese and Western Medicine affiliated with Shanghai University of Traditional Chinese Medicine. We will also seek potential patients through posters, Internet advertisements, and the official microblog and WeChat platforms. All participants are aged 18 to 65 years. We define 10 years as an interval, and the number of participants in each interval is almost equal.

### Inclusion criteria

The inclusion criteria are as follows:
Duration of low back pain as the main symptom for at least 3 monthsPain lasting more 20 min per time and at least once per monthAged between 18 and 65 years, male or femaleVolunteer to take part in the study and sign the informed consent formPromise not to receive other related therapy during the period of treatmentCapable of complying with the intervention and follow-up assessment

### Exclusion criteria

The exclusion criteria are as follows:
Chronic low back pain caused by local disease (e.g., lumbar fracture, lumbar tumor, lumbar tuberculosis, lumbar spine surgery or trauma)Sciatica, myelopathy, displacement, or radiculopathy due to lumbar intervertebral disc disorders or spondylolisthesisSevere primary disease such as cardiovascular, lung, kidney, and hematopoietic diseaseOngoing treatment within 5 days prior to inclusionMental disorderPregnant womanPatients not suitable for nuclear magnetic resonance examination

### Dropout and suspension criteria

Patients have the right to withdraw for any reason during the study period according to the Patient Management Protection Rules. The following conditions are considered as withdrawal criteria: (1) patient does not implement the protocol treatment on schedule; (2) participation in other treatments during the trial; (3) intolerable adverse events; and (4) lost to follow-up. In addition, if severe poor efficacy or adverse reactions occur during the trial, the trial will be forcibly suspended immediately.

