### Interventions

The participants will receive a total of 24 treatments in 3 months. The therapists must have 10 years of experience with Tuina treatment or be skillful in health care education for the participants. In addition, they are required to have passed a clinical test to make sure that the consistency of the trial is administered. It should be emphasized that some other treatments for low back pain during the trial will be forbidden, which includes medication therapy, surgery, drug injections, acupuncture, moxibustion, and physical therapy. If the subjects receive any other treatment, it will be recorded the changeable each time he arrives.

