#### Statistical analyses

The intention-to-treat principle will be followed in the primary data analysis with IBM SPSS Statistics for Windows version 21.0 software by statisticians who are blinded to the group allocation. The baseline characteristics will be expressed with descriptive statistics for the two groups, which are reported as the mean ± standard deviation. A Kolmogorov-Smirnov test with Lilliefors correction will be used to analyze all quantitative variables to determine whether they follow a normal distribution. Parametric statistics (Tukey test) or nonparametric statistics (Wilcoxon rank-sum test) will be used for the within- and between-group analyses in accordance with the results of the homogeneity and normality analyses. When initial homogeneity and normality of data distribution are found, repeated measures analysis of variance (ANOVA) and ANOVA with Bonferroni *post hoc* statistics will be used to analyze within and between groups. The Friedman test and Kruskal-Wallis test will be used when initial homogeneity but not normality of data distribution is found. If the initial homogeneity is not found, a linear mixed model will be adjusted for the baseline value. Adverse events in each group will be documented as percentage for safety assessments using the chi-square test or Fisher’s exact test. The statistical significance is defined as *P* < 0.05, and the 95% confidence interval will be reported.

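### The plan as written does not secure the intention-to-treat analysis it states: non-adherence is grouped with loss to follow-up as grounds for withdrawal, and the default analyses need complete visits

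*Protocol article*

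**What the plan says.** All references are to the protocol article.

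- **Dropout and suspension criteria.** The withdrawal list begins "1) patient does not implement the protocol treatment on schedule; (2) participation in other treatments during the trial" and continues "3) intolerable adverse events; and (4) lost to follow-up". Four different events carry one label. The section does not say what happens to outcome assessment afterwards.
- **Interventions.** Other treatments for low back pain are forbidden during the trial, but the stated consequence is only this: "If the subjects receive any other treatment, it will be recorded the changeable each time he arrives". Withdrawal is not mentioned.
- **Inclusion criteria and Safety evaluation.** The patient's promise to avoid other related therapy covers the treatment period. For the six months of follow-up, patients are to have routine lumbar care only, and they are telephoned at months 6 and 9.
- **Statistical analyses.** "The intention-to-treat principle will be followed in the primary data analysis". Three branches follow. Homogeneous, normal data go to "repeated measures analysis of variance (ANOVA) and ANOVA with Bonferroni" post hoc comparisons. Homogeneous, non-normal data go to Friedman and Kruskal-Wallis tests. If initial homogeneity is not found, a linear mixed model adjusted for baseline is used.
- **Abstract.** Outcomes are assessed up to and "during 6 months and 9 months of follow-up by repeated measures analysis of variance", with no alternative named.
- **Outcome measurements and Sample size calculation.** There are six time points, of which five are after baseline. Eighty patients per group are planned, with 10% dropout allowed for.

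**The concern.** Intention to treat needs two things: outcomes collected from all randomised patients as far as possible, and an analysis that keeps them in their allocated group. The plan leaves both open.

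A patient who misses sessions, takes another treatment or stops because of an adverse event can usually still fill in a questionnaire. A patient who is lost to follow-up cannot. Putting both under withdrawal invites sites to stop assessing the first kind as well. Participants and therapists are unblinded, the outcomes are self-reported, and the two arms ask different things of patients. Adherence and care-seeking could therefore differ by arm and depend on how the patient is doing. If those patients' later scores are not collected, or are dropped, the comparison loses the protection of randomisation. Scores never collected cannot be recovered at analysis.

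The default analyses add to this. A patient with a single missed visit can fall out of the repeated measures analysis altogether, even when the other five scores are on file.

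**Working it through.** **1. The passages side by side**

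| Question | Dropout criteria | Interventions | Statistical analyses |
|---|---|---|---|
| What happens to a patient who takes other treatment? | Withdrawn | Treatment recorded at each attendance | Intention to treat |
| Are withdrawn patients assessed to month 9? | Not stated | Recording implies continued attendance | Not stated |
| Are they analysed as randomised? | Not stated | Not stated | Implied by the principle, not stated for this group |

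The period of the restriction also varies: the treatment period in the Inclusion criteria, the trial in the Dropout criteria and Interventions, and routine care only during follow-up in the Safety evaluation. Site staff cannot tell from this whether a patient who takes other treatment in month 5 stays under assessment.

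**2. What each analysis branch does with a missed visit**

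- Classical repeated measures ANOVA in SPSS deletes any patient with a missing time point.
- The Friedman test needs complete blocks, so it does the same. A Kruskal-Wallis test at one visit needs only that visit's value.
- The linear mixed model uses partial records. It is reached only if initial homogeneity is not found, which is the less expected case after randomisation.

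**3. Illustration of the loss of patients**

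From the plan: 80 per arm, 10% dropout, five post-baseline visits. Assumed: a fraction m of values missing at each visit, independently, on top of the 10%; baseline complete; nothing imputed.

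- The plan's own allowance: 80 × 0.90 = 72 per arm.
- Complete cases = 72 × (1 − m)^5.
- m = 3%: 72 × 0.97^5 = 72 × 0.859 = 61.8, about 62 (77% of 80).
- m = 5%: 72 × 0.95^5 = 72 × 0.774 = 55.7, about 56 (70% of 80).

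**4. Illustration of power**

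The plan gives no ODI effect or SD. Its sample size rests on response rates of 95% and 85%, so those rates give no power for the ODI analysis. (Nor do they give 80 per arm: a two-sided calculation needs 141, or 157 after dropout. That is a separate matter and this point does not depend on it.) An effect of 0.47 SD is assumed because it gives 80% power at 72 per arm. Two-sided t-test at 5%:

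| Per arm | Power at 0.47 SD |
|---|---|
| 72 | 80% |
| 62 | 74% |
| 56 | 69% |

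**5. Illustration of bias (all inputs assumed)**

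Suppose 15% of the education arm and 5% of the Tuina arm go unanalysed after taking other treatment, and their ODI is 10 points worse than that of patients retained. Dropping them lowers the education mean by 0.15 × 10 = 1.5 and the Tuina mean by 0.05 × 10 = 0.5. The arm difference shifts by 1.5 − 0.5 = 1.0 point on the 0 to 100 scale, in favour of education. The reverse pattern shifts it the other way.

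A simulation points the same way. It assumed 10% random withdrawal under Tuina and about 17% under education, likelier with a worse month 1 score. In units of the between-patient SD, a true difference of 0 became about +0.15 among those kept, and a true difference of −0.40 became about −0.25.

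**The case against.** A reader might infer that the plan excludes non-adherent patients and so delivers a complete-case analysis in place of intention to treat. The document does not support that reading.

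- The Dropout criteria do not say that withdrawal ends assessment or removes anyone from the analysis. The Interventions section, by recording other treatment at each attendance, suggests that such patients continue.
- Repeated measures ANOVA is one of three branches, and the third already keeps partial records.
- Complete-case analysis follows only if nothing is imputed. A missing-data rule may sit in an analysis plan that is not shown, and its absence here is no finding.
- The figures are soft. The 0.47 SD is not in the document. The 10% is described as a maximum, so adding further missingness to it may be pessimistic. With 3% per visit and no separate dropout, 80 × 0.97^5 leaves about 69 per arm and 78% power. Missed visits that cluster in the same patients would cost less than independent ones.
- The differing periods for the ban on other treatment are partly a matter of reading, since one is an eligibility promise and another stands under the three-month intervention.

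All of this stands, and it limits the point to what the plan fails to secure. The contradiction between withdrawing and merely recording is still on the page. So is the choice of complete-record methods as the two default branches, one of them the only method named in the abstract. Nor can imputation fully replace outcomes that were never collected.

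**Conclusion.** The point holds in this limited form: the plan states intention to treat, but its withdrawal criteria and default analyses do not secure it. That conclusion comes from the text and needs no numerical assumption beyond how the named procedures treat missing visits.

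The size cannot be fixed from the document. Apart from the 10% dropout, every input to the illustration is assumed. On those inputs, 62 to 56 complete cases per arm remain out of 80, and power at 0.47 SD goes from 80% to between 74% and 69%. Bias could go in either direction, and its size depends on who is withdrawn and why. The example of 1 ODI point shows the mechanism and is not a forecast.

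**What to change.** 1. Reconcile the Inclusion criteria, Dropout and suspension criteria, Interventions and Safety evaluation sections on other treatment: which period is covered, and whether it leads to withdrawal or to recording. Which clinical rule applies is for the investigators to settle; none is proposed here.
2. State that meeting a withdrawal criterion does not by itself end outcome assessment. Keep collecting ODI, VAS and SF-36 to month 9 from every patient who consents and can be reached.
3. Make the baseline-adjusted linear mixed model, on all available data and by allocated group, the primary analysis in all cases and not only when initial homogeneity is not found. Align the Abstract with it.

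Step 2 matters most, because a mixed model cannot make up for outcomes that a site stopped collecting for reasons the data do not show.

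**Cost.** A short amendment and revised statistical wording. Telephone contacts at months 6 and 9 are already planned, but assessments at months 1 to 3 in patients no longer attending would need extra contacts and questionnaires. Recruitment began in June 2019, so patients already withdrawn may lack later data; their number by arm should be reported.

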### Randomization

The randomization sequence will be generated by a random number generator (IBM SPSS Statistics version 21.0 software; IBM Corp., Armonk, NY, USA), which will be sent to a therapist with an opaque envelope numbered sequentially. The therapist will sequentially open random-allocation envelopes and allocate the participants accordingly. Eligible patients will be randomized to the Tuina group or the health care education group, with 80 patients in each group.

### Blinding

Participants and therapists will not be blinded to treatment allocation, owing to the limitation of the therapies. Interventionists will be masked to the participants’ outcome measurements. The evaluators, data managers, and statisticians will be blinded to the group allocation in the outcome evaluation procedure and data analysis for the sake of reducing the risk of bias.

### Interventions

The participants will receive a total of 24 treatments in 3 months. The therapists must have 10 years of experience with Tuina treatment or be skillful in health care education for the participants. In addition, they are required to have passed a clinical test to make sure that the consistency of the trial is administered. It should be emphasized that some other treatments for low back pain during the trial will be forbidden, which includes medication therapy, surgery, drug injections, acupuncture, moxibustion, and physical therapy. If the subjects receive any other treatment, it will be recorded the changeable each time he arrives.

### Tuina group

The tendons and bones theory of traditional Chinese medicine summarizes the physiology and pathology of physical movement. The relationship between tendons and bones in the human body is inseparable. During body movement, the muscles will contract to produce force and transfer it to the bone with the help of ligaments or tendons. At the same time, the bone can efficiently process the force to different parts of ligaments and tendons, resulting in a coordinated motion pattern. Coordination of tendons and bones is the main basis for maintaining the dynamic balance of the spine and joints of the body. Tuina of “restrict bone and harmonize joints” intends to restore the harmonious relationship between tendons and bones by manipulation of the low back with the therapist’s hands. The specific process is outlined in the subsections below.

### Step 1: local manipulation

First, the patients are in a prone position. The doctor stands on the side of the patient with the method of rolling the Bladder meridians on both sides of the spine, which is applied for 3 to 5 min. The waist will be focused on to manipulate preferentially and then using the same technique on the patient’s buttocks and lower limbs at the same time. It plays the role of relaxing sinews and activating collaterals with the theory of traditional Chinese medicine. Second, the physician will perform the manipulation on the patient’s waist and the posterolateral side of the lower limbs by pressing, kneading, plucking, and so forth for 5 to 7 min, which can relieve the cramping of the muscles. The doctors press the acupoints, including Mingmen (DU04), Shenshu (BL23), Yaoyangguan (DU03), Huantiao (GB30), Weizhong (BL40), Chengshan (BL57), and Ashi points, with the elbow or the thumb to achieve Deqi sensation, which is commonly regarded as an indicator of manipulation efficacy [31–34]. Last, scrubbing manipulation will be used to dilate the heat with the palms. In conclusion, the above content refers to therapeutic manipulation for sinew injury.

